### Secondary objectives

We will compare overall participation rates in the third round with those in the first and second round and will compare participation rates in previous participants and non-participants of the first and/or second round. In addition, we will evaluate the complication rate of FIT screening, including follow-up colonoscopy in FIT-positives, and compare these to the results of the first and second round of screening. Also we will evaluate the number and cancer stage of interval cancers in the cohort during the 3 consecutive rounds.

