## Test results

The test result will be sent to the participant and his or her general practitioner by regular mail. In case of a positive test result, the participant will be invited for a consultation at the screening center at the Academic Medical Center in Amsterdam or the Flevo Hospital in Almere. During the consultation, the need for a follow-up colonoscopy will be discussed and the individuals exclusion criteria and/or contra-indications for colonoscopy are checked. Test positive Invitees with end-stage disease and a life-expectancy of less than 5 years, and those who have had a complete colonoscopy in the previous two years, will not be invited for colonosopy. In absence of contra-indications, a colonoscopy will be planned within two weeks after the consultation. In case of a negative test result, no follow up is advised.

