### Cancer registry

All invitees are linked to The Netherlands Cancer Registry, which collects data of new cancer patients, such as tumor type, incidence date and stage [19]. Using this registry, we can identify interval carcinomas in the three consecutive screening rounds.

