### Data analysis

Participation rate is defined as the number of invitees returning a FIT relative to the number of all eligible invitees. The third round participation rate will be compared with those of the two previous screening rounds. Participation rates in subgroups of participants and non-participants of previous screening rounds will be compared. Among third round invitees the following subgroups can be defined: (1) non-participants in the first and the second round; (2) participants in the first and the second round; (3) invitees who participated in the first but did not in the second round; (4) second round participants who did not participate in the first round (5) second round participants who were not invited for the first round (6) second round non-participants who were not invited for the first round and (7) first time invitees. Screening yield is calculated by dividing the total number of participants with detected advanced neoplasia by the number of participants (per-protocol analysis) and the total number of invitees (intention-to-screen analysis). Advanced neoplasia is defined as a CRC or an advanced adenoma. An advanced adenoma is defined as an adenoma ≥ 10 mm, an adenoma with ≥ 25% villous histology or an adenoma with high grade dysplasia. We will express participation rates and diagnostic yield as proportions and present estimates with corresponding confidence intervals. We will compare proportions by Chi-square statistic. We will evaluate the number and stage of interval cancers. Interval cancers will be defined as the proportion of cancer diagnosed in first and second round participants outside the screening. Interval cancers will be identified via cross-linkage of the screening pilot with the Dutch cancer registry. Cancer stage at diagnosis and location will be retrieved via the registry. Descriptive statistics will be used to analyze the interval cancers. Chi-square test statistic will be used to analyze the distribution of cancer stage and location between screen detected cancers of the first, second and third round and interval cancers.

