### Implications

This study will provide information on participation and yield in the third round of a FIT- based CRC screening program. Participation rate and determinants of participants will be compared with the first and the second screening round. This study will also provide information on interval cancers in FIT based screening, in a third round of biannual pilot screening. As FIT is generally preferred over guiaic-FOBT in most countries FIT will become the test of choice. The study results will enable us to estimate the effectiveness of a FIT-based CRC screening program with 2-yearly rounds, such as the one that will be implemented in the Netherlands in 2013.

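### The printed interval-cancer definition requires no negative FIT, end of interval, colorectal site or denominator, and its round coverage needs reconciling with other sections

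*Protocol article*

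**What the plan says.** The Data analysis section gives an explicit rule: "Interval cancers will be defined as the proportion of cancer diagnosed in first and second round participants outside the screening". Cases are to be found by linkage to the cancer registry and described by number and stage. Their stage and location are then compared by chi-square with cancers detected by screening in rounds 1, 2 and 3.

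Three other sections bear on scope:

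- Secondary objectives: the study will "evaluate the number and cancer stage of interval cancers in the cohort during the 3 consecutive rounds".
- Cancer registry, on who is covered by the linkage: "All invitees are linked to The Netherlands Cancer Registry, which collects data of new cancer patients, such as tumor type, incidence date and stage". It adds that with this source "we can identify interval carcinomas in the three consecutive screening rounds".
- Implications: "This study will also provide information on interval cancers in FIT based screening, in a third round of biannual pilot screening".

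Two sections bear on FIT-positive people. Study design and population says that earlier positives are not invited again. Test results says that some positives do not go on to colonoscopy: those with end-stage disease and limited life expectancy, and "those who have had a complete colonoscopy in the previous two years, will not be invited for colonosopy".

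**The concern.** An interval cancer in a FIT programme is meant to capture disease that appears after a reassuring test and before the next one is offered. The printed rule lacks the elements that make it so.

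- **No FIT result.** A cancer in someone whose FIT was positive but who was not fully investigated meets the rule, although the test did not miss that person.
- **No end to the interval.** A round 1 participant who ignored the round 2 invitation and is diagnosed in year 3 or 4 meets the rule, although the two-year interval has closed.
- **No site and no denominator.** The rule says cancer, not CRC, although the registry records tumour type. It also calls a set of cases a proportion without saying of what.
- **Scope.** People who first take part in round 3 can never contribute a case, yet other sections speak of three rounds or of the third.

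Mixing these groups blurs what the interval-cancer count means. The same case set is one arm of the stage and location comparison, so any misclassification carries into that test.

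**Working it through.** The article states no interval-cancer count, rate or sample size, so there is no figure of the plan's own to reproduce. The check is mainly textual, with one calculation.

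**1. Lapsed participants**

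Inputs: 86% of round 1 participants took part again in round 2 (Background). Round 2 came two years after round 1, and round 3 comes four years after round 1 (Primary objective).

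Assumptions: an interval of *w* years after each test; all round 1 participants counted here were re-invited; no deaths, moves or earlier cancers.

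Per 100 round 1 participants followed from round 1 to round 3:

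- Person-years counted by the rule as printed: 100 × 4 = 400.
- Person-years inside the interval with *w* = 2: 100 × 2 + 86 × 2 = 372.
- Outside: 400 − 372 = 28, and 28/400 = 7.0% of the total. Relative to the valid time, 28/372 = 7.5%.

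The window is my assumption. For *w* between 2 and 4 years, the share outside is 14 × (4 − *w*)/400:

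| Assumed window | Person-years outside | Share of 400 |
|---|---|---|
| 2 years | 28 | 7.0% |
| 2.5 years | 21 | 5.25% |
| 3 years | 14 | 3.5% |

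This is person-time, not cancers, and it stops at round 3 because the rule gives no cut-off date.

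**2. FIT-positive people**

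Cancers found at the follow-up colonoscopy are screen-detected, so the rule already leaves them out. What remains is cancer in positives who had no completed work-up, and cancer appearing after that work-up. Nothing in the rule excludes either. The number cannot be derived, because the article gives neither FIT positivity nor colonoscopy uptake. The 5.5% in the Background is a detection rate of advanced neoplasia, not a positivity rate.

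**3. Scope, section by section**

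| Section | Rounds named |
|---|---|
| Data analysis (definition) | participants of rounds 1 and 2 |
| Secondary objectives | the three rounds |
| Cancer registry | the three rounds |
| Implications | a third round |

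Three rounds contain two completed intervals, 1 to 2 and 2 to 3, and participants of rounds 1 and 2 are the people at risk in them. The Secondary objectives wording can be read that way. The Implications wording fits that reading poorly. A round 3 participant who also took part earlier stays covered; only someone whose first participation is in round 3 is left out.

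**The case against.** The strongest reply has four parts.

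*The article is condensed, and linkage rules usually sit in the full protocol.* That would answer a missing detail. Here a definition is printed, and followed as printed it admits the wrong cases. The reply lowers the urgency but does not remove the defect.

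*Earlier FIT-positives may already be out.* If the linked invitees are only those of this round, people who tested positive before are not among them. The Data analysis section, however, describes linking the screening pilot, which may be wider. The account of positives who do not go to colonoscopy is also written for the present round, and the article does not say how positives in rounds 1 and 2 were handled. So this route to misclassification is open on the text but not shown to have occurred.

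*Limiting the definition to rounds 1 and 2 may be deliberate,* since cancers after round 3 need follow-up beyond the 2011 invitations. This stands. A reader might infer that the definition flatly contradicts the objective; the text supports only an inconsistency that needs reconciling.

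*The outcome is secondary and largely descriptive.* This also stands. The registry supplies incidence dates and the programme generates FIT results and invitations, so cases could still be classified properly at analysis.

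**Conclusion.** The definition is badly fixed and should be corrected before the linked data are analysed. As written, it counts as interval cancers those in FIT-positives without a completed work-up and those in round 1 participants who skipped round 2. Both groups then enter the comparison with screen-detected cancers.

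The only part that the article allows one to size is the lapsed group: 14% of round 1 participants, and about 7% of round 1 participants' person-time over four years. That rests on an assumed two-year window and the simplifications listed above.

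A reader might go further and infer that the interval-cancer result will be wrong, that the count is inflated by a large fraction, or that FIT sensitivity will be understated by a known amount. The article does not support this. It gives no interval-cancer count, positivity or colonoscopy uptake, and it promises no sensitivity estimate. What can be said is that the result is open to misclassification of unknown size. The primary outcomes, participation and yield, are unaffected.

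**What to change.** 1. Define an interval cancer as a CRC diagnosed after a negative FIT and before that person's next screening invitation is due.
2. State the denominator, for example the FIT-negative participants of the round in question, and report the count alongside it.
3. Report separately cancers after a positive FIT that were not diagnosed through the screening work-up, and cancers in lapsed participants. Keep both out of the interval arm of the stage and location comparison.
4. Say which population is linked: this round's invitees or everyone in the pilot.
5. Reconcile the Secondary objectives, Cancer registry, Data analysis and Implications sections on the interval after round 3. Either restrict the objective to the two completed intervals, or state a registry follow-up cut-off after round 3.

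Items 1 to 4 cost wording and a date rule applied to linkage already planned. Under item 5, restricting the objective costs nothing. Covering a full interval after round 3 would delay that result by about two years plus any registry lag.

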### Implications

This study will provide information on participation and yield in the third round of a FIT- based CRC screening program. Participation rate and determinants of participants will be compared with the first and the second screening round. This study will also provide information on interval cancers in FIT based screening, in a third round of biannual pilot screening. As FIT is generally preferred over guiaic-FOBT in most countries FIT will become the test of choice. The study results will enable us to estimate the effectiveness of a FIT-based CRC screening program with 2-yearly rounds, such as the one that will be implemented in the Netherlands in 2013.

## Abbreviations

CRC, Colorectal cancer; FOBT, Fecal occult blood test; EU, European union; FIT, Fecal immunochemical test.
